### Dose escalation

This study will use a Bayesian Optimal Interval design (BOIN design) with a target dose-limiting toxicity (DLT) rate of 30% and three pre-specified activity levels [15]. The three pre-specified activity levels of the [^177^Lu]Lu-PSMA-617 administration are: level one: three GBq, level two: six GBq and level three: nine GBq. Planned enrolment of a maximum of 18 patients or fewer (depending on the observed rate of DLTs) will be used to evaluate safety and tolerability. The DLT rate is calculated as the number of patients experiencing a DLT during the current dose divided by the total number of patients treated at the current dose.

To accelerate dose escalation, based on the knowledge of limited toxicity with a single administration [9], the trial starts with a cohort size of one patient per activity level. A cohort is expanded to three patients if the first DLT is observed. If no DLT is observed at activity levels one and two, the cohort size at the highest activity level (level three) will also be expanded to three patients. If no DLT is observed at all, the trial is terminated at the last activity level if the upper limit of the 95% binomial confidence interval (CI) is below 0.5 and the last activity (level three: nine GBq) is then selected as the MTD. This means that when zero out of six patients have a DLT at activity level three, the trial is terminated, because the 95% CI then ranges from zero to 0.46.

If a DLT is observed, the decision to expand the cohort and retain the current activity, to de-escalate, to escalate or to stop the trial is based on the pre-specified activity escalation and de-escalation boundaries for a DLT rate of 30% (λe = 0.236, λd = 0.358) and maximum sample size according to the BOIN design principles. The resulting decision rules are presented in Table 3. In addition to these decision rules, the following rules for safety are embedded. In level one, the trial will be stopped for safety if 2/3 or 3/3 patients experience a DLT. In activity level two and three, the activity will be eliminated according to the rules specified in the last row of Table 3. Elimination of a activity indicates that the current activity and higher activities will not be investigated anymore and the trial continues on a lower activity level.

**Table 3 Tab3:** Escalation, de-escalation, elimination and stopping boundaries for each level depending on the number of patients with DLT

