Action	**The number of patients treated at each dose**																	
	**1**	**2**	**3**	**4**	**5**	**6**	**7**	**8**	**9**	**10**	**11**	**12**	**13**	**14**	**15**	**16**	**17**	**18**
Level 1:																		
Stop the trial if # of DLT > =	NA	NA	2	3	3	4	4	4	5	5	6	6	6	7	7	7	8	8
Level 2 and 3:																		
Escalate if # of DLT < =	0	0	0	0	1	1	1	1	2	2	2	2	3	3	3	3	4	4
De-escalate if # of DLT > =	1	1	2	2	2	3	3	3	4	4	4	5	5	6	6	6	7	7
Eliminate dose if # of DLT > =	NA	NA	3	4	5	5	6	6	7	7	7	8	8	9	9	10	10	11

*DLT* Dose limiting toxicity, *NA* Not applicable, # number

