This study protocol has some limitations: Firstly, the BOIN-design is chosen for more flexibility in: the chosen target toxicity rate and cohort size and has a better performance in comparison to 3 + 3 design [15]. However the downside is that a tighter de-escalation boundary to impose a higher safety requirement and decreasing the risk of overdosing, may also reduce the percentage of correct selection and the number of patients allocated to the MTD.

Secondly, the choice to start with three GBq was based on earlier safety and efficacy studies, where they used a administered activity of six GBq [^177^Lu]Lu-PSMA-617 for multiple times in one single patient [31, 32]. Because this study is a phase I study combining EBRT with one cycle of [^177^Lu]Lu-PSMA-617, we chose to start with half of the activity (three GBq), out of precaution. The use of nine GBq has been proven to be safe [33], thus a starting dose of three GBq to a maximum of nine GBq is well grounded in our opinion. However, the best dose to administer may be higher, lower or somewhere in between the selected activity of three, six and nine GBq. Lastly, in this phase I study patients only get one cycle of [^177^Lu]Lu-PSMA-617 to evaluate the toxicity, whilst in current practice, mCRPC patients receive multiple cycle of [^177^Lu]Lu-PSMA-617 with limited toxicities. The study by Rahbar et al. showed that response (PSA reduction ≥ 50%) is only or mostly seen after the second cycle of [^177^Lu]Lu-PSMA-617 in men with mCRPC [9]. As this is a phase I study concerning treatment naïve prostate cancer patients with less tumour load, we think that one cycle of [^177^Lu]Lu-PSMA-617 is well grounded and can give additional anti-tumour effect. From an oncological point of view, adding additional treatment cycles will probably increase efficacy, without adding additional toxicity (based on salvage CRPC data). Upon successful dose-finding, adding cycles may be explored in subsequent research.

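### With no DLTs the plan names 9 GBq the MTD, but 0 of 6 at the top level neither locates nor excludes the 30% target rate

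*Protocol article*

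**What the plan says.** All references are to the Protocol article.

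- **Primary objectives** (Method): the aim is to determine the MTD of one cycle among three, six or nine GBq, using the BOIN design. A DLT is any CTCAE v5.0 toxicity of grade three or higher from the start of EBRT to 3 months after its completion.
- **Dose escalation**: the design has a "target dose-limiting toxicity (DLT) rate of 30% and three pre-specified activity levels". The decision "boundaries for a DLT rate of 30% (λe = 0.236, λd = 0.358") apply once a DLT has been observed, and Table 3 tabulates them.
- **Dose escalation, path without DLTs**: "the trial starts with a cohort size of one patient per activity level". If levels one and two show no DLT, "the cohort size at the highest activity level (level three) will also be expanded to three patients". If no DLT is seen at all, the trial stops once the upper 95% limit at level three falls below 0.5. The article says this happens at 0 of 6, with an interval of zero to 0.46. Then "the last activity (level three: nine GBq) is then selected as the MTD".
- **Discussion, limitations**: "the best dose to administer may be higher, lower or somewhere in between the selected activity of three, six and nine GBq".

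The article makes no provision for a result in which the MTD is not reached.

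**The concern.** In a design with a 30% target, the MTD is the activity whose DLT rate is judged closest to that target. On the path without DLTs nothing locates that rate. The stopping trigger, an upper limit below 0.5, is a tolerability screen and not an estimate of where 30% lies. Escalation ends because there is no fourth level, not because toxicity has reached the target.

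The primary conclusion would then claim more than was learned. A reader who sees that the MTD is 9 GBq from a trial with a 30% target may take 9 GBq as an established ceiling. The data would say only that six men at that activity had no DLT. The Discussion concedes that the best dose may be higher, but does not connect this with the label, and it makes further work conditional on successful dose-finding.

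**Working it through.** **Inputs** (Dose escalation unless noted): target rate 0.30; boundaries 0.236 and 0.358; path without DLTs of 1 man at level one, 1 at level two and 6 at level three; stopping criterion of an upper 95% limit below 0.5; stated interval for 0 of 6 of 0 to 0.46.

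**1. Reproduce the plan's own figures.** The exact two-sided 95% upper limit for 0 of n is 1 − 0.025^(1/n).
- n = 5: 0.522
- n = 6: 0.459, which matches the stated 0.46

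Six is therefore the smallest n that meets the criterion. With the values φ1 = 0.6 × 0.30 = 0.18 and φ2 = 1.4 × 0.30 = 0.42 (assumed, as the article does not state them), the BOIN boundaries are 0.2365 and 0.3585. These agree with the stated values. The figures are right; the question is what they support.

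**2. Set 0 of 6 against the target.**
- The observed rate is 0/6 = 0, below 0.236. In Table 3 the row "Escalate if # of DLT <"= has the entry 1 at n = 6, so both 0 and 1 DLT fall in the escalate zone.
- The interval of 0 to 0.459 contains 0.30.
- P(0 of 6 | true rate 0.30) = 0.70^6 = 0.118.
- P(0 of 6 | true rate 0.358) = 0.642^6 = 0.070.

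So 0 of 6 gives no evidence that the target was reached and does not exclude it. For zero DLTs to exclude 30%, the upper limit would have to fall below 0.30. That needs 0 of 11 with a two-sided limit (0.285) or 0 of 9 with a one-sided 95% limit (0.283).

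**3. How likely is this path?** It uses 1 + 1 + 6 = 8 men. If the per-patient DLT rate p is the same at every level (an assumption), P(no DLT) = (1 − p)^8:

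| Assumed p | P(no DLT in 8 men) |
|---|---|
| 2% | 0.85 |
| 5% | 0.66 |
| 10% | 0.43 |
| 15% | 0.27 |

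The probability exceeds one half only if p is below 1 − 0.5^(1/8) = 8.3%. If rates rise with activity, the product is (1 − p1)(1 − p2)(1 − p3)^6:
- 3%, 5%, 8%: 0.56
- 5%, 10%, 15%: 0.32

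**4. Is zero DLTs the right dividing line?** No. One DLT in six at level three is 1/6 = 0.167, also below 0.236. It is equally a result that the design reads as below target. A corrected label should therefore depend on the escalation boundary and not on whether any DLT occurred.

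**The case against.** **This is an ordinary selection rule.** The objective names a closed set of three activities. Choosing the top one after no DLTs is prespecified and transparent, and the interval is printed beside the rule. This stands. Neither the choice of level nor any computed figure is at fault, only the name given to the result.

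**Table 3 does not govern this path.** The article introduces the boundaries for the case in which a DLT has been observed, gives the path without DLTs its own rule, and has no level above three. This also stands, so the two rules do not contradict each other. The boundary serves here only as the design's own yardstick for a rate below target.

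**Two stronger readings are tempting, and the documents support neither.**
- A reader might infer that zero DLTs prove 9 GBq lies below the 30% rate. The plan's own interval contains 0.30, and 0 of 6 occurs 11.8% of the time at a true rate of 30%. Even under a uniform prior, which the plan does not specify, the probability of a rate above 0.30 after 0 of 6 is 0.70^7 = 8%.
- A reader might infer that the protocol itself predicts no DLTs as the likeliest outcome. The Hypothesis section does expect few severe events. But its figure of below 5% for grade three toxicity applies to each evaluated parameter in each treatment week, on RTOG criteria, for EBRT with ADT. The DLT counts any type of event per patient on CTCAE criteria over the whole window. No per-patient rate is given.

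**The harm is partly disclosed.** The Discussion limitation and the printed interval would help a careful reader. They do not change what the primary conclusion would say.

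**Conclusion.** The point holds as a matter of labelling and interpretation, and it is worth correcting because it concerns the primary conclusion. After 0 of 6, the data support the statement that 9 GBq was the highest activity tested and met the stopping criterion, with a DLT rate between 0 and 0.46. They do not support the statement that the MTD has been determined.

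The interval and the comparison with 0.236 rest only on the article's own figures. The probability of meeting the situation, from 85% down to 27% for rates of 2% to 15%, rests on an assumed per-patient rate that is equal across levels. That range is enough to call the path plausible, not to call it the likeliest. No conclusion is drawn about which activity is appropriate.

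**What to change.** Leave the stopping point and the selection of the level as they are, and change the reporting rule. Suggested text for Dose escalation:

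*If the trial ends at level three with an observed DLT rate at that level at or below the escalation boundary (0.236), including zero DLTs, the result is reported as: MTD not reached within the activities tested; 9 GBq is the highest activity tested. The observed DLT rate and its exact 95% confidence interval are given (for 0 of 6: 0 to 0.46).*

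Suggested addition to Primary objectives:

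*If no MTD is reached within the activities tested, the highest activity tested is reported with its DLT rate and interval.*

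Reporting the interval also makes clear that the phrase does not claim the true rate is below 30%.

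Cost: two sentences, with no change to enrolment, stopping or treatment. The downside is a slightly less favourable primary conclusion.

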### Temporary inclusion stop

After the last inclusion of each cohort, the inclusion will temporarily freeze until 1 month after the last EBRT of that cohort has been given. The occurrence of acute CTCAE grade three toxicity from EBRT and ADT is known to be limited (see also section 2: Hypothesis). When a patient has not demonstrated any grade three or higher acute toxicity well into the recovery phase at 1 month after the last EBRT fraction, the chance of newly developing grade three acute toxicity is extremely small and the primary endpoint will be considered negative for the purpose of dose escalation for subsequent patients. This means that, independent from the EBRT scheme, there will also be at least 2 months follow-up after the [^177^Lu]Lu-PSMA-617 administration for each patient.

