**Fig. 2 Fig2:**
[figure not shown]
Study design. At the start of the treatment patients receive adjuvant hormone therapy (ADT) at most one month prior to the start of external beam radiation therapy (EBRT) and will continue during EBRT. Adjuvant hormone therapy is then continued as adjuvant treatment up to the advised total duration of 3 years (provided that its toxicity remains acceptable). In week two of EBRT, patients also receive one concurrent cycle of systemic [^177^Lu]Lu-PSMA-617 (Lu-PSMA) as part of the study procedure

**Table 1 Tab1:** Inclusion and exclusion criteria

Inclusion criteria	Exclusion criteria
Histologically proven prostate cancer	Inability to comply to study procedures
cT2-4, partly determined by MRI	Inability to adhere to radiation safety measures in hospital or at home
N1, determined by LND/SNP and/or PSMA PET/CT	Inability to undergo the required biodistribution scans
iM0, determined by PSMA PET/CT	Prior or current malignant disease with potential impact on treatment outcome or survival
Accepted for curative intent treatment with EBRT of the prostate and regional nodes + three years ADT	Prior treatment with EBRT
Visually PSMA-positive primary tumour and nodes, largest lesion > average liver accumulation	Prior treatment with ADT, already initiated > one month before the start of EBRT
WHO performance score 0–1	Prior treatment with radionuclide therapies, [^177^Lu]Lu-PSMA-617 or other
Age > 18 years	Reduced bone marrow reserve (Hb < 6 mmol/L, Leukocytes < 2.5 10E9/L, or Platelets < 100 10E9/L not older than one month before start of EBRT)
For patients who have partners of childbearing potential: Willingness to use a method of birth control with adequate barrier protection during the study and for six months after the study drug administration	Reduced renal function (GFR < 60 ml/min/1,73m^2^ not older than one month before start of EBRT)
Signed written informed consent	Reduced salivary gland function (history of prior salivary gland disease)
	Urinary problems requiring pre-treatment with ADT^a^

*ADT* Androgen deprivation therapy, *CT* Computed Tomography, *EBRT* External beam radiation therapy, *GRF* Glomerular filtration rate, *Hb* Hemoglobulin, *LND* Lymph node dissection, *Lu-PSMA* Lutetium PSMA, *MRI* Magnetic resonance imaging, *PET* Positron emission tomography, *PSMA* Prostate specific membrane antigen, *SNP* Single node procedure, *WHO* World health organization

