### Hypothesis

The hypothesis of this phase I study is that combining EBRT and ADT (in accordance to current standard of care) with one cycle of systemic [^177^Lu]Lu-PSMA-617 delivered in week two of EBRT, in treatment naïve patients with PSMA-positive N1M0 prostate cancer will not induce significant additional toxicity. It is important to exclude significant additional toxicity, because this could potentially lead to interruption of the standard curative intent treatment. To evaluate toxicity of a multimodal treatment, the toxicities of the separate components need to be considered.

The toxicity profile of ADT has been reported extensively, and includes e.g. fatigue, sexual dysfunction, gynecomastia, flushes and depression [10]. Beyond these acute issues, there is increasing awareness of the long-term effects. ADT leads to adverse changes in body weight, body composition, insulin resistance and serum cholesterols, together known as the “metabolic syndrome”, with changes already observed after only 12–24 weeks and largely persistent after the end of treatment [11].

The acute toxicity of EBRT of the prostate and pelvic nodes with concurrent ADT has also been reported extensively, for example in the PIVOTAL study in 2018 [12]. These data illustrate that grade 1–2 acute toxicities according to Radiation Therapy Oncology Group (RTOG) criteria are common, occurring in up to 30% for the gastrointestinal tract and up to 40% for the bladder, with their peak incidence at the end of EBRT. However, grade three acute toxicities are rare, below five % in all treatment weeks for all evaluated parameters. The late toxicity of pelvic EBRT was also reported in the same study [12], which reports that occurrence of late grade one toxicities according to CTCAE criteria are common, occurring in up to about 70% for the gastrointestinal tract as well as the bladder. Late grade two toxicities are rare, below 20% up to 2 years for the gastrointestinal tract and below 30% up to 2 years for the bladder. CTCAE grade one toxicities increase during at least 2 years after treatment, and their incidence at 6 months should be considered a relatively poor indicator. Whilst grade two toxicities show much less increase over time, and their incidence at 6 months is a reasonable indicator for toxicity later on. Finally, late grade three toxicities hardly occurred (< 5%).

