### Primary objectives

To determine the maximum tolerated dose (MTD) of one cycle [^177^Lu]Lu-PSMA-617 (three, six, or nine GBq) when administered in combination with standard EBRT and ADT. MTD will be determined according to the Bayesian Optimal Interval (BOIN)-design (see section 2: Dose escalation) [15]. Dose-limiting toxicity (DLT) is defined as an acute toxicity, occurring from the start of EBRT up to 3 months after completion of EBRT, according to CTCAE v. 5.0 grade three or higher of any type. As CTCAE grade three or higher toxicities are very limited in EBRT and ADT combination therapy, this is considered to be a suitable endpoint for tolerability in this study (see hypothesis above). Relation of acute CTCAE grade three toxicity or higher to the study treatment is determined by the principal investigators, and will be verified by a safety committee prior to escalation to a higher dose level.

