### Treatment

#### Standard treatment scheme

Included patients will receive standard of care EBRT and ADT with curative intent according to current clinical guidelines. EBRT involves 35 fractions intensity modulated radiotherapy (IMRT), 5 days per week over 7 weeks, delivering physical doses of 70–77 Gy to the prostate (and seminal vesicles if applicable), 60–63.35 Gy to macroscopic lymph node metastases, and 52.5–56.35 Gy to RTOG-based elective pelvic nodal fields expanded to include all detected nodal metastases (Fig. 3). ADT consists of 3-monthly subcutaneous depots of 10.8 mg gosereline or equivalent treatment, with 4 weeks bicalutamide 50 mg orally from 2 weeks before till 2 weeks after the first administration. ADT is standard initiated at most 1 month prior to the start of EBRT (counting from the start of bicalutamide), is continued during EBRT, and is then continued as adjuvant treatment up to the advised total duration of 3 years (provided that its toxicity remains acceptable).

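### The promised 2 months of follow-up after Lu-PSMA before escalation holds if EBRT is completed, but the freeze rule does not secure it for a patient who stops EBRT well short of 35 fractions

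*Protocol article*

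**What the plan says.** All references are to the protocol article.

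- **Freeze (Temporary inclusion stop).** After the last inclusion of a cohort, "the inclusion will temporarily freeze until 1 month after the last EBRT of that cohort has been given".
- **Negative call (same section).** If a patient has had no grade three or higher acute toxicity by 1 month after the last fraction, "the primary endpoint will be considered negative for the purpose of dose escalation for subsequent patients".
- **Property claimed (same section).** As a consequence of this rule, "independent from the EBRT scheme, there will also be at least 2 months follow-up after the" Lu-PSMA administration, and this is said of each patient.
- **EBRT (Standard treatment scheme).** "EBRT involves 35 fractions intensity modulated radiotherapy (IMRT), 5 days per week over 7 weeks". The physical dose is given as a range, but the number of fractions and the duration are fixed.
- **Lu-PSMA timing (Fig. 2 legend).** "In week two of EBRT, patients also receive one concurrent cycle of systemic" Lu-PSMA.
- **DLT window (Primary objectives).** Acute toxicity "occurring from the start of EBRT up to 3 months after completion of EBRT".
- **Cohort size (Dose escalation).** "the trial starts with a cohort size of one patient per activity level".
- **Withdrawal of individual patients.** Patients may leave at any time, and no further study follow-up is asked for after withdrawal.

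**The concern.** The section treats 2 months of observation after Lu-PSMA as a safety property that holds for each patient whatever the EBRT. Yet no clock in the section starts at Lu-PSMA. Both the freeze and the negative call run from the last EBRT fraction, so the time observed after Lu-PSMA depends directly on how long EBRT continues after it.

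The matter arises for a patient who receives Lu-PSMA, then stops EBRT permanently and early, and has no DLT. At levels one and two the cohort starts with one patient, so no other patient's later last fraction holds the freeze in place. Inclusion could then reopen after less observation of the investigational product than the section says every patient will have.

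**Working it through.** **Inputs**
- 35 fractions, 5 per week (Standard treatment scheme).
- Lu-PSMA in week two. With a Monday start as day 1, the weekdays of week two are days 8 to 12.
- Freeze ends 1 month after the last fraction given (Temporary inclusion stop).
- Assumptions: a month is 30 days, 2 months is 61 days, and there are no treatment gaps or holidays. The article does not define a month in days.

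**Formulas**
- Day of the n-th fraction: L(n) = 7 × floor((n − 1)/5) + ((n − 1) mod 5) + 1.
- Days from Lu-PSMA to the end of the freeze: F = L(n) + 30 − U, where U is the Lu-PSMA day (8 to 12).

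**Step 1: reproduce the stated figure.** For n = 35, L = 7 × 6 + 4 + 1 = 47. Then F = 47 + 30 − 12 = 65 to 47 + 30 − 8 = 69 days. This is 4 to 8 days above 61, so the statement holds for the planned course. Other start weekdays put the last fraction on day 49 and give 65 to 71 days. With a 28-day month the shortest case is 63 days.

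**Step 2: fewer fractions given.**

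| Fractions given | Day of last fraction | F for U = 12 to 8 (days) |
|---|---|---|
| 35 | 47 | 65–69 |
| 30 | 40 | 58–62 |
| 25 | 33 | 51–55 |
| 20 | 26 | 44–48 |
| 15 | 19 | 37–41 |

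**Step 3: fractions needed to reach 61 days.** The condition F ≥ 61 means L(n) ≥ 31 + U.
- U = 8: day 39 or later, 29 fractions.
- U = 9: day 40 or later, 30 fractions.
- U = 10, 11 or 12: days 41, 42 or 43 or later. Day 43 is the next treatment day after the weekend, so 31 fractions.

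The 2-month figure is therefore lost when EBRT stops more than about 4 to 6 fractions early (35 − 31 = 4, 35 − 29 = 6). Letting the month run from 28 to 31 days widens the requirement to 28 to 33 fractions.

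**The case against.** The strongest reply is that the EBRT scheme most naturally means the planned fractionation, and that the article describes one length only: 35 fractions over 7 weeks. For that the statement is true. Handling of early EBRT stop and evaluability are commonly left to the full protocol, which is not shown. This much stands: the article's silence on early stopping is not in itself a fault. But the statement also speaks of each patient and is presented as a consequence of the freeze rule, and the rule as written does not deliver it.

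The Hypothesis section warns that added toxicity is a concern because "this could potentially lead to interruption of the standard curative intent treatment". That is weak support here. A temporary gap moves the last fraction later and lengthens the interval; only a permanent stop shortens it.

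A reader might infer more than the documents support:

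- **That the statement fails for anyone who stops early.** It does not. About 29 to 31 fractions still reach 61 days.
- **That escalation typically follows about 5 weeks after dosing.** This needs EBRT to stop within days of Lu-PSMA. A stop after 10 fractions gives 12 + 30 − 12 = 30 to 12 + 30 − 8 = 34 days, in a one-patient cohort and without a DLT. Even then this marks reopened inclusion. The next patient receives Lu-PSMA only in week two of their own EBRT, at least 7 days after starting it.
- **That the final DLT rate is biased downward.** This is not shown. The negative call is for escalation only; the DLT window and the visits at three and 6 months continue after the freeze lifts. A stop caused by grade three or higher toxicity judged related to study treatment would count as a DLT. Stops for other reasons need not reflect poor tolerance.
- **That a five-week EBRT scheme breaks the rule in this trial.** The Discussion names five weeks only as a future option.
- **That the DLT window has no end after an early stop.** The Temporary inclusion stop section uses the last fraction as its anchor, and the same reading could apply to the window. The article does not say so, which calls for reconciliation and no more.

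**Conclusion.** The concern holds in a limited form. For the planned 7-week course the 2-month minimum is met, with a margin of 4 to 8 days. It is not met for a patient without a DLT who receives fewer than about 29 to 31 of the 35 fractions. The shortfall against 61 days is 6 to 10 days after 25 fractions (61 − 55 to 61 − 51) and 13 to 17 days after 20 (61 − 48 to 61 − 44). At levels one and two, while the cohort is one patient, that patient's stop date alone would set the reopening of inclusion. In a larger cohort the latest last fraction governs, which may mask the shortfall.

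This is more than an omitted detail, because a stated rule does not secure a stated safety property. How often such a stop would occur cannot be judged from the article. The figures assume a Monday start, a 30-day month, uninterrupted fractions, and week two counted from the first fraction.

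**What to change.** Reconcile the freeze rule with the 2-month statement in Temporary inclusion stop. Two options would do this using only intervals the protocol already states:

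1. The freeze lifts, and the negative call for escalation is made, only when both 1 month after the last EBRT fraction and 2 months after Lu-PSMA have passed.
2. The 2-month statement is limited to patients who complete the planned EBRT.

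The choice belongs to the investigators and the safety committee; no new interval is proposed here. Primary objectives, Withdrawal of individual patients, Temporary inclusion stop and Standard treatment scheme should also be made to agree on how a patient who stops EBRT early is treated.

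The cost is one sentence. Nothing changes for patients who complete EBRT, since 65 to 69 days already exceeds both intervals. Under option 1, an early stop in a one-patient cohort would prolong the freeze by the shortfall: 6 to 10 days after 25 fractions, 13 to 17 days after 20. Option 2 adds no delay but gives up the assurance for those patients.
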